### Randomization

We will adopt the web-based allocation system using the University Medical Information Network (UMIN), which is one of the data centers that run as a public institution in Japan. By entering the information about the patient, investigators will be able to know the allocation results immediately.

The allocation table, which was created by stratified block randomized by the trial statistician, is registered in the UMIN. The block size is concealed to all investigators involved in this study. We have adopted stratification factors as follows:

•the presence of ossification of the posterior longitudinal ligament (OPLL) (yes/no)

•implementation of high-dose methylprednisolone treatment according to the NASCIS2 protocol (yes/no)

•preexisting gait disturbance due to myelopathy

•degree of canal compromise (50% or more/less than 50% canal compromise)

Preexisting gait disturbance due to myelopathy will be determined by the attending spine surgeon before randomization, based on thorough patients’ history and available medical record. Gait disturbance attributable to other causes (for example, trauma, osteoarthritis, and paralysis after stroke) will be excluded.

Presence of severe canal compromise (50% or more canal compromise) will be assessed by the attending spine surgeon based on mid-sagittal MR images obtained at admission. For patients presented with OPLL, mid-sagittal reconstruction CT images or plain radiographs of the cervical spine will be used to calculate the degree of canal compromise.

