### Sample size

For this exploratory trial, the sample size was determined primarily based on feasibility. We assumed that it is feasible to enroll approximately 100 patients (50 patients per group) during the planned study period. As there is no valid data to indicate the optimal endpoint to evaluate the neurological and functional recovery of SCI patients, we selected three candidate endpoints as the primary endpoint: 1) the change from the baseline to one year after the admission in the ASIA motor score; 2) the proportion of patients who regained the ability to walk 100 meters without human assistance and 3) the total score of the Spinal Cord Independence Measure (SCIM) version 3.

We need 45 patients per group when the difference to be detected in the ASIA motor score between the groups is 12 points and the common standard deviation is 20. Additionally, we expect that the percentage of ambulatory patients one year after the injury will increase from 50% to 80%. To detect this difference, we need 39 patients for each group. With regard to the SCIM, there are few data that can be used as a basis for sample size calculation. For the reasons above, we set the sample size to be 50 patients per group. All calculations assume an 80% power at a two-tailed significance level of 0.05.

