### Statistical methods

All analyses will be based on an intention-to-treat principal, and will be performed with two-sided *P*-values considered significant when they are below 0.05. For a detailed analysis, the statistician will make a statistical analysis plan before the data lock, as indicated below:

1) Primary endpoint:

•ASIA motor score

Calculate the difference one year after the baseline, and compare the two groups using a *t*-test

•The proportion of patients who regained the ability to walk

Calculate the rate of patients who can walk one year after the baseline, and compare the two groups using the chi-square test

•SCIM

Compare the differences in the SCIM after one year.

2) Secondary endpoint:

Compare the differences in the WISCI II, SF-36 and EQ-5D. For the SF-36, we plan to use only the total points, and not to compare each domain.

3) Safety:

We will compare the rates of adverse events between the groups. In particular, in patients that are moved out of the surgical standby group, we will compare the ratio of the occurrence of adverse events with those in the patients in the early operation group.

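### Randomisation is stratified on four factors, but the primary t-test and chi-square test ignore them; to the extent the factors predict outcome, the tests are conservative and lose some power

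*Protocol article*

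**What the plan says.** Under Randomization, the allocation table is built by stratified blocks, with the block size concealed from investigators. The four stratification factors are OPLL (yes/no), NASCIS-2 methylprednisolone (yes/no), "preexisting gait disturbance due to myelopathy", and "degree of canal compromise (50% or more/less than 50% canal compromise").

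Under Statistical methods, the change in ASIA motor score is compared by a t-test. For walking the text is: "Calculate the rate of patients who can walk one year after the baseline, and compare the two groups using the chi-square test". SCIM is to be compared after one year with no test named. The same section says that a statistical analysis plan will be written before data lock along the lines it lists.

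No stratified or covariate-adjusted primary analysis is mentioned. The four factors reappear only under Planned subgroup analyses.

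Under Sample size: "We need 45 patients per group when the difference to be detected in the ASIA motor score between the groups is 12 points". This takes the SD as 20 in both arms. For walking, 50% vs 80%: "To detect this difference, we need 39 patients for each group". Power is set at 80% and alpha at 0.05 two-sided throughout. The trial is set at 50 per group.

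**The concern.** Blocking within strata forces the arms to be nearly balanced on the four factors. Whatever those factors contribute to outcome therefore largely cancels from the difference between arms. An unadjusted t-test or chi-square test still counts that contribution as random noise. Its standard error is then larger than the real sampling variation of the difference under this design, the p-value is too large and the confidence interval too wide.

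At stake is efficiency. The sample size was set by feasibility, so precision that costs no extra patients is worth having. The protocol also names the tests and has the later plan follow them, so this is a stated choice that a compliant analysis plan would carry forward.

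**Working it through.** **1. The plan's own figures reproduce.**
- ASIA: n = 2(1.960 + 0.842)² × (20/12)² = 43.6, so 44 by the normal approximation. The exact t-test calculation gives 44.6, so 45, as stated.
- Walking, pooled variance, no continuity correction: n = [1.960√(2 × 0.65 × 0.35) + 0.842√(0.25 + 0.16)]² / 0.30² = 38.5, so 39, as stated.
- At 50 per group, power is about 0.84 for the t-test and 0.89 for the chi-square test.

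**2. Size of the mismatch in the limit.** Let the factors jointly explain a share R² of the ASIA variance. With perfect balance, the true standard error of the difference is √(1 − R²) times the one the t-test uses, and type I error is about 2[1 − Φ(1.96/√(1 − R²))].
- At 50 per group the t-test uses about 20√(2/50) = 4.0 points. At R² = 0.25 the true value would be 4.0 × √0.75 = 3.46.
- Type I error at R² = 0.10/0.15/0.25/0.40: 3.9/3.4/2.4/1.1%.

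Balance is not perfect here. Four binary factors make 16 strata, 100/16 is about 6 patients per stratum, and many blocks stay incomplete. The real effect is therefore smaller than this limit, and simulation is needed.

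**3. Simulation.** Inputs from the protocol: N = 100, 1:1 allocation, difference 12, SD 20, walking 50% vs 80%. Assumed, because the protocol does not give them: prevalences of 35/30/20/50%, blocks of 4, independent factors, and their prognostic strength.

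| Share of ASIA variance explained | t-test type I error | Power lost against the adjusted model |
|---|---|---|
| 10% | 4.1% | about 2 points |
| 15% | 3.9% | about 4 points |
| 25% | 3.1% | about 5 points |
| 40% | 1.9% | about 9 points |

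| Odds ratio of every factor for walking | Chi-square type I error | Power lost |
|---|---|---|
| 1.5 | 5.3% | about 0 points |
| 2 | 4.6% | about 1 point |
| 3 | 3.7% | about 3 points |
| 4 | 2.9% | about 4 points |

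If only gait disturbance matters, with an odds ratio of 3, the chi-square test stays at about 5% and power is about 0.90 with or without adjustment.

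**4. Sensitivity and control.** A second set of runs used prevalences of 40/20/25/50% and blocks of 2 and 4.
- t-test type I error was 4.0–4.1% at R² 0.1, 3.3% at 0.2 and 2.3–2.4% at 0.3.
- Models with the four factors as main effects gave 4.4–5.6% in every scenario.
- ASIA power, unadjusted to adjusted, went from about 0.85 to 0.87 (R² 0.1), 0.86–0.87 to 0.91–0.92 (0.2) and 0.88 to 0.94 (0.3).
- With unstratified randomisation and equally strong factors (R² 0.3, odds ratio 3), the unadjusted tests were at 5.1% (t-test) and 5.8% (chi-square). With stratified blocks they fell to 2.3–2.4% and 3.8–4.0%. The conservatism comes from stratifying and then ignoring the strata.

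**The case against.** The strongest reply is that the protocol never calls the factors prognostic and gives no strength for any of them. The subgroup section treats gait disturbance and canal compromise as possible modifiers of the treatment effect, which is a different property. This stands: the size of the effect is conditional, and for walking it is negligible when the factors are weak.

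Four stronger readings are tempting, and the documents do not support them:
- *The planned tests run below 5%.* Not as a fact. The chi-square test shows little or no shortfall at odds ratios of 1.5 to 2 per factor.
- *Gait disturbance, a natural predictor of walking, is enough to cause the problem.* Alone at an odds ratio of 3 it has almost no effect. A visible shortfall needs all four factors to be strong together.
- *The trial is underpowered or its sample size is wrong.* The figures of 45 and 39 reproduce, and the unadjusted tests exceed 80% power at 50 per group. The loss is relative to an adjusted analysis.
- *The results would be invalid.* The error is conservative and leaves the estimated difference unbiased.

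It can also be said that adjustment belongs in the unseen analysis plan and that the trial calls itself exploratory. Silence in the article would indeed be no finding. But the article names unadjusted tests and has the plan follow them, so only part of this reply stands. An exploratory purpose makes correct interval widths more useful, not less.

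**Conclusion.** The mismatch is real, and its direction is certain if the factors predict outcome: standard errors too wide, tests conservative, power lost. The size rests on assumed prevalences, block size and prognostic strength. It shows first in the ASIA t-test, already when the factors explain about 10% of variance, and becomes material at about 25% (type I error near 3%, about 5 points of power). For the chi-square test it becomes visible only at odds ratios of about 3 for every factor (3.7%, about 3 points). SCIM has no named test, so the mismatch strictly concerns the ASIA motor score and walking. This is an efficiency gain worth taking, not a threat to validity.

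**What to change.** In Statistical methods:
- Make the primary ASIA analysis a linear model for the change in motor score on arm plus the four stratification factors as main effects.
- Make the primary walking analysis a regression on arm plus the same four factors, reported as a standardised risk difference with a 95% confidence interval.
- Name the same adjusted linear model for SCIM.
- Use main effects and not the 16 cells, which hold about 6 patients each and are too sparse for a fully stratified analysis.
- Keep the unadjusted t-test and chi-square test as sensitivity analyses.

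The cost is wording before data lock. The factors are determined before randomisation, so no new data are needed. Adjusting for the admission ASIA motor score may also improve precision, but it was not a stratification factor; that is a separate recommendation and not part of this mismatch.

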#### Delayed surgery

Patients allocated to the delayed surgery group will receive conservative treatment consisting of early mobilization and intensive rehabilitation for at least two weeks after the injury. Surgical decompression will be performed by the same team as in the early surgery group at any time later than two weeks after the injury when the physician thinks the timing is appropriate. Physicians will be allowed to treat patients non-surgically as long as the patients can achieve independent ambulation.

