### Adverse events

The occurrence of pre-specified adverse events will be also assessed. Adverse events will be gathered from patients themselves and from the patient record review. The *a priori* defined adverse events are: worsening of paralysis in the upper extremities, worsening of paralysis in the lower extremities, reoperation, use of a respirator (more than one week), tracheostomy, sepsis, pneumonia, acute respiratory distress syndrome, atelectasis, other respiratory complications, wound infection (superficial), wound infection (deep), urinary tract infection, other infections, gastrointestinal bleeding, peptic ulcer, ileus, acute myocardial infarction, other cardiac events, pulmonary embolism, cerebrovascular complication, liver dysfunction/disease, renal dysfunction/disease, delirium, depression, other complications and death.

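### The emphasised safety comparison appears to set a part of the delayed arm, formed after randomisation, against the whole early arm; it should be descriptive, not tested

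*Protocol article*

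**What the plan says.** All references are to the Protocol article.

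- **Statistical methods, opening sentence.** "All analyses will be based on an intention-to-treat principal", and they "will be performed with two-sided *P*-values considered significant when they are below 0.05". No analysis is exempted.
- **Statistical methods, Safety, first sentence.** "We will compare the rates of adverse events between the groups".
- **Statistical methods, Safety, second sentence.** Introduced as a point of particular interest: "in patients that are moved out of the surgical standby group, we will compare the ratio of the occurrence of adverse events". The comparator is the early arm, without restriction. The standby group is not defined, no test is named, and nothing marks the comparison as descriptive.
- **Delayed surgery.** After at least two weeks of conservative care, decompression takes place "when the physician thinks the timing is appropriate". Also, "Physicians will be allowed to treat patients non-surgically as long as the patients can achieve independent ambulation".
- **Sample size.** 50 patients per group.

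**The concern.** The two sides of the second safety comparison are formed by different rules. The comparator is the early arm as randomised. The other side is most naturally a part of the delayed arm, picked out by what happened to those patients later. The Delayed surgery section gives two routes by which delayed patients separate: the physician's judgement about when to operate, and regained independent walking, which permits no operation at all. Both act after randomisation, and regained walking is itself a recovery outcome.

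The early arm is not divided in the same way. Its patients who would have recovered while waiting stay in the comparator, as do those who would not. The contrast can therefore show a difference when the two strategies carry the same risk. A lower-risk subset would make delay look safer, and a higher-risk subset would make it look more harmful. Under the general 0.05 rule, either result could be reported as a significant safety difference, in the comparison to which the text gives emphasis.

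**Working it through.** **Plan's own figure.** The plan gives no figure for this comparison: no subset size, no expected adverse-event rate and no power. The sample sizes in the Sample size section concern efficacy and do not bear on it.

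**Inputs.** From the protocol: 50 per group, and two-sided 0.05. Assumed: the same true adverse-event risk p0 in both arms; a subset of m of the 50 delayed patients; and a gap g, the risk in the subset minus the risk in the rest of the delayed arm.

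**Expected false difference.** Let s be the subset risk and r = s − g the risk in the rest. The delayed arm must average p0:

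(m/50) × s + (1 − m/50) × (s − g) = p0, so s = p0 + (1 − m/50) × g.

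The expected difference from the early arm is therefore (1 − m/50) × g, provided that both s and r lie between 0 and 100%.

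- m = 10: 0.8 × g, that is 8 points for a 10-point gap and 16 for a 20-point gap.
- m = 25: 0.5 × g, that is 5 and 10 points.
- m = 40: 0.2 × g, that is 2 and 4 points.

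**False-positive rate.** Exact enumeration of two binomials (50 early patients at risk p0, m delayed patients at risk s), chi-square test without continuity correction at two-sided 0.05, with p0 = 40%. Where a cell has two figures, the first is for a lower-risk subset and the second for a higher-risk subset.

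| m | no gap | 10-point gap | 20-point gap | 40-point gap |
|---|---|---|---|---|
| 10 | 5.1% | 6.8% / 8.3% | 13.9% / 16.6% | 54.0% / 49.1% |
| 25 | 5.6% | 7.2% / 8.0% | 13.4% / 14.7% | 41.2% / 40.5% |
| 40 | 5.1% | 5.5% / 5.6% | 6.7% / 7.0% | 12.1% / 12.3% |

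All randomised patients, 50 against 50: 5.2%.

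**How extreme the last column is.** With m = 10, a 40-point gap means subset against rest risks of 8% against 48%, or 72% against 32%. With m = 25 it means 20% against 60%, or the reverse. These cells mark an outer limit, not an expectation.

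**Lower base risk.** At p0 = 20% and a 20-point gap, the rates are 4.1% / 22.4% (m = 10), 18.1% / 17.1% (m = 25) and 7.2% / 7.3% (m = 40). For m = 10 the lower-risk figure is no higher than with no gap (also 4.1%), because a small subset at low risk has little room to show a deficit. A 40-point lower-risk gap with m = 10 is impossible there: 20% + 0.8 × (−40%) = −12%.

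**Second check, with milder selection.** A simulation took 30% overall risk, half of the patients at two to three times the risk of the others, and high-risk patients three times or one third as likely to enter a subset of 20% to 60% of the delayed arm. The subset's expected rate became 35% to 37.5%, or 22.5% to 25%, against 30% in the early arm. The false-positive rate was about 5% to 11%, and about 5% when selection was unrelated to risk.

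**The case against.** The strongest objection is that the phrase is undefined and occurs once. If it is a clumsy name for everyone allocated to delayed surgery, the comparison is randomised and nothing is wrong. This stands as a limit: a reader might infer that the bias arises whatever the phrase means, and the text does not support that. But the whole-arm reading makes the second sentence repeat the first and leaves the words about moving out with no work to do, so a subset is the natural reading.

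A second objection is that an analysis plan is announced and could define the subset and say how it is analysed. It could, but a definition would not make a subset chosen after randomisation comparable with an undivided early arm. The choice of comparison is stated here, not left open. No test is named for safety, but the opening sentence applies its threshold to all analyses.

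Third, a reader might infer that patients leave standby because their paralysis worsens. The Adverse events section does list "worsening of paralysis in the upper extremities, worsening of paralysis in the lower extremities", so the event would then define the subset in which it is counted. No section describes rescue surgery or early crossover, however, so that route is conjecture and the point does not rest on it. The two routes in the Delayed surgery section are in the text, although their link to adverse-event risk is an assumption.

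Finally, the trial is described as exploratory, has an independent safety monitoring board and plans the valid comparison. All of this stands, and it keeps the point minor.

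**Conclusion.** The point holds in a limited form. On the natural reading, the second safety sentence sets a group selected after randomisation against an unselected arm. That conflicts with the section's own intention-to-treat rule while falling under its significance threshold. The trial's main safety result is not affected, because all randomised patients are compared first; the documents do not support reading this as a flaw in the overall safety conclusion.

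The size rests wholly on assumptions. At 40% risk in both arms and a 10 to 20 point gap, the false-positive rate is about 6% to 17%. It is close to 5% when selection is weak or the subset is most of the arm. Rates of 40% to 54% appear only under extreme selection and should not be quoted as likely. Nor does the effect hold at every base risk, as the 20% case shows. This is worth changing because the change is nearly free, not because the harm is shown to be large.

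**What to change.** Keep the first safety sentence, and state that the comparison of all randomised patients by allocated group is the only tested safety contrast. Replace the second sentence with, for example: *Adverse events in the delayed group will also be described by surgical course (operated or not, and when). This description is non-randomised and exploratory, and no P-value against the early group will be given.*

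If the whole delayed arm was meant, this wording still serves, because the first sentence already covers that comparison.

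The cost is one sentence and one descriptive table; no sample size changes. The table needs the date of any operation in the delayed group. The Early surgery section already has surgical details recorded on a web form, and it is assumed that the same can be done for delayed patients. The downside is that there will be no direct test of patients who leave standby against early surgery, and some rows may be small. A descriptive table can still be over-read, which is why the label matters.

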### Planned subgroup analyses

Predefined subgroup analyses will be performed in patients with or without OPLL. These will include high-dose methylprednisolone treatment, preexisting gait disturbance and severe canal compromise (> 50% canal compromise). Based on our previous study, we hypothesize that early surgical decompression will be beneficial in patients with preexisting gait disturbance and those with severe canal compromise.

### Ethical issues

The study protocol was approved by the local ethics committees of all participating hospitals and will be done in accordance with the Declaration of Helsinki. The study will be overseen by an independent safety monitoring board. All participants will give written informed consent before entry.

Ethical approval was obtained from all participating hospitals. The results will be disseminated via the usual scientific forums, including peer-reviewed publications and presentations at international conferences.

## Discussion

Despite intensive basic and clinical research, an effective treatment for cervical SCI has not been established. In the presence of preexisting canal stenosis, the role of surgical decompression and its optimal timing continue to be subjects of intense debate. Addressing the issue of the timing of surgical intervention is critical in that, if the timing of surgery has no effect on the patient’s outcome, then all patients can initially be treated non-surgically and surgery can be delayed for weeks or even months after the injury without compromising the patient’s recovery [6]. On the other hand, if early surgical decompression is proven to be beneficial, drastic changes in the medical service system, including logistics, should be made to ensure that all SCI patients receive early surgery.

In conducting clinical studies on SCI, the heterogeneity of the study population can be a major obstacle, especially in the acute phase. SCI patients vary greatly in the severity of paralysis and neurological prognosis. Clinical studies including patients with various degrees of neurological injury may have insufficient power. Therefore, in this study, we will focus on patients with ASIA C status. In a recent review, the consensus of experts was that it is reasonable to consider early surgical decompression in patients with profound neurologic deficit (ASIA C) and spinal canal stenosis without fracture or instability. On the other hand, those with a less severe deficit (ASIA D) can be treated with initial observation with surgery potentially performed at a later date [6]. We will exclude patients with ASIA B status, because these patients are often difficult to distinguish from ASIA A patients at the time of admission.

The information available regarding the window of opportunity or therapeutic window in human SCI is imprecise [24] and the definition of ‘early surgery’ has not yet been well established. Although the ideal cutoff time at which surgery provides potential neuroprotection is not known, the most intensively investigated times in the prior studies were 24 and 72 hours. In this study, we have adopted a cutoff at twenty-two hours after admission mainly for practical and logistic reasons. Twenty-four hours after admission is considered to be necessary and sufficient to safely perform the initial evaluation of patients and summon the operating team for emergency surgery. In this study, we adopted the time of admission as a reference, since the time of injury sometimes remains conjectural.

The OSCIS study is designed to provide evidence of the potential benefit of early surgical decompression over a wait-and-see strategy. We believe that the results of this trial will have a substantial impact on the management of cervical SCI.

